#### 2.4.3. Fitness Tracker

Physical activity is assessed daily by supplying each patient uses a commercial fitness tracker (Fitbit charge 3™ (Fitbit Inc., San Francisco) that will be linked to her smartphone (54). Study personnel assists the patients and – if required – their associate to install the smartphone app and to setup the measurements. The patients are requested to transcribe the measurements of their fitness tracker into their study diary weekly. Those values are shown in **Table 3**.

**Table 3 T3:** Measurements with the fitness tracker.

Description	Abbreviation	Registration interval	Unit
**Core stats**		**Daily**	
Steps taken		Daily	Count
Resting heart rate	RHR	Daily	Beats per minute
Calories burned	Cal	Daily	Kcal
**Workout stats**		**Real-time**	
Elapsed time		Real-time	Minute
Distance covered		Real-time	Km
Calories burned		Real-time	Kcal
Average heart rate	øHR	Real-time	Beats per minute
Maximum heart rate	HRmax	Real-time	Beats per minute

### 2.5 Body Composition

#### 2.5.1. Bioelectrical Impedance Analysis

The body composition will be determined based on bioelectrical impedance analysis (BIA) (TANITA scale™, Tanita Europe BV, Stuttgart). The test person stands barefoot on a body scale and holds sensors in both hands. Using the impedance between the four measuring points, numerous data can be collected that provide information on the muscle, fat, bone and water content of the whole body and individual compartments. Bioimpedance analysis is routinely used in the context of nutritional advice and sports medicine, but it can also shed light into disease processes, such as hemodialysis patients (55) (**Table 4**). When accessible, the body composition will also be estimated by using routine CT scans of the study patients as previously published (56).

**Table 4 T4:** Measurements by scale and bioimpedance analysis.

Item	Unit
Weight	kg
Total body fat	%
Total muscle mass	kg
Bone mass	kg
Body-Mass-Index	Kg/m²
Basal metabolic rate	kcal
Metabolic age	years
Total body water	%
Visceral fat	kg
Segmental muscle mass in arms, legs, and torso	kg
Segmental body fat in arms, legs, and torso	%

#### 2.5.2 Plicometry (Calipometry)

Plicometry allows a standardized estimate of the body fat status which can change under influences such as sport, chemotherapy or cancer (57–60). In the BEGYN study, fat distribution is assessed using the skinfold measurement using the 3 point-method (triceps, suprailiac skinfold, and thigh) according to Jackson and Pollock (61). (**Figure 2**). The total body subcutaneous fat tissue (in kg) was estimated from the plicometry measurements using the formula (61):

$$\text{Total}\;\text{body}\;\mathrm{subcutaneous}\;\text{fat}\;(\text{kg})\;=\;[(4.95/(1.0994921-(0.0009929^{*}\text{S})+(0.0000023^{*}{\text{S}}^{2})-(0.0001392^{*}\text{age}\{\text{in years}\})))-4.5{]}^{*}100.$$

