### 2.3 Clinical Assessment

Routine assessment during quarterly follow-up visits includes an anamnesis focused on potential side effects of antineoplastic therapies, measuring the body weight and blood pressure.

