**Figure 2 f2:**
[figure not shown]
Plicometry sites of measurement (58, 59). Skinfold measurement using the 3 point-method (1 = triceps, 2 = suprailiac skinfold; 3 = thigh).

S is the sum of the skinfold thicknesses measured at the triceps, the suprailiac skinfold and the thigh.

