The BEGYN study also has some limitations, such as the single center approach. However, the data will serve as a basis for designing future multicenter studies. In example, the results of the BEGYN study might help focusing the highly detailed immunophenotyping regarding the characterization of leukocyte subsets, mRNA transcripts and cytokines to the most promising variables in future study protocols. One further limitation of the study is that the quality of self-assessments may underlie intra-individual and inter-individual variations when filling out the self-assessment diary (e.g. daily documentation of physical activities, weekly read outs of the measurements of the fitness tracker etc.). Due to the need of serial measurements of the body composition, ethical concerns on X-ray exposure were the reason to use bioimpedance analysis and plicometry rather than Dual-energy X-ray absorptiometry, which is regarded as the gold standard (106). With regard to the known limitations of bioimpedance analysis and plicometry, we will compare the intra-individual relative changes over time instead of absolute values (107). In addition, we will further extend the data by estimating the body composition from the routine CT scans of the study patients (56). The BEGYN study is an observational study, thus potential causal relationships must be interpreted carefully. Ethical concerns would not allow randomizing patients into a group that would not be encouraged to exercise since this would conflict with the high evidence guidelines. However, the BEGYN study might help defining valid methods of continuous registration of physical activity for future studies to compare the role of various types of exercise, e.g., training of strength versus endurance.

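### The plicometry formula is labelled as kilograms of fat but has no body-mass term and returns a value on a percentage scale

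*Protocol article*

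**What the plan says.** Section 2.5.2 (Plicometry) introduces the derived variable with the words "The total body subcutaneous fat tissue (in kg) was estimated from the plicometry measurements using the formula". The left side of the equation repeats the unit kg. The right side begins "4.95/(1.0994921-(0.0009929" and continues with S, S squared and age. The quotient then has 4.5 subtracted and is multiplied by 100. The note under Figure 2 defines the only other input: "S is the sum of the skinfold thicknesses measured at the triceps, the suprailiac skinfold and the thigh". No later step brings in body weight.

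Weight is available. Section 2.3 lists "measuring the body weight and blood pressure" among the routine assessments at the quarterly follow-up visits, and Table 4 records weight in kg with the bioimpedance measurements. Table 4 gives bioimpedance total body fat in %.

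The limitations paragraph at the end of section 3.1.4 says how these measurements will be used: "we will compare the intra-individual relative changes over time instead of absolute values".

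**The concern.** A mass of fat has to depend on how much the person weighs, or on some other measure of body size that stands in for weight. This formula takes three skinfold thicknesses and an age. Two women of the same age and skinfold sum, one weighing 55 kg and the other 95 kg, would be credited with the same number of kilograms of fat.

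Sections 2.2 and 2.5.2 make plicometry part of every visit, and section 3.1.4 gives it, with bioimpedance, as the substitute for dual-energy X-ray absorptiometry. An analyst who follows section 2.5.2 as written would tabulate a percentage under a kilogram heading, next to a bioimpedance fat value in %. A within-patient change could then be described as gain or loss of fat mass when it is a change in fat proportion. The two differ whenever body weight changes.

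**Working it through.** **Inputs.** From section 2.5.2: the constants of the formula, with S and age as the only variables. From the note under Figure 2: S is a sum of three skinfolds. The article gives no worked plicometry value, so there is no figure of its own to reproduce. The values of S, age and weight below are assumptions for illustration. The unit of S is not stated in the text, and mm is assumed.

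**Formula as printed.**

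D = 1.0994921 − 0.0009929 × S + 0.0000023 × S² − 0.0001392 × age

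Output = (4.95/D − 4.5) × 100

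**Step 1: the scale of the outer expression.**
- D = 1.10: 4.95/1.10 = 4.5, so the output is 0.
- D = 0.90: 4.95/0.90 = 5.5, so the output is 100.

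This is a 0 to 100 scale and needs no assumed inputs. For S from 20 to 150 mm and age from 30 to 75 years, D runs from 1.076 down to 0.992 and the output from 9.9 to 49.1.

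**Step 2: two worked values at age 55.**
- S = 60: D = 1.0994921 − 0.0595740 + 0.0082800 − 0.0076560 = 1.0405; output 25.7.
- S = 100: D = 1.0994921 − 0.0992900 + 0.0230000 − 0.0076560 = 1.0155; output 37.4.

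Neither value changes with body weight.

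**Step 3: size of the discrepancy if the output is read as kg.** If the output is a percentage of body mass, then mass = output/100 × weight, and the printed figure differs from it by the factor 100/weight. For S = 60, age 55 (output 25.7):

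| Assumed weight | Fat mass implied by 25.7% | Printed figure ÷ fat mass |
|---|---|---|
| 55 kg | 14.1 kg | 1.82 |
| 70 kg | 18.0 kg | 1.43 |
| 95 kg | 24.4 kg | 1.05 |
| 100 kg | 25.7 kg | 1.00 |
| 120 kg | 30.9 kg | 0.83 |

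The two readings coincide only at 100 kg. Below that weight the kg label overstates fat mass, and above it the label understates it.

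**Step 4: relative change over one year (age 55 to 56).**

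| Assumed course | Change in formula output | Change in implied fat mass |
|---|---|---|
| S stays at 80; weight 70 to 77 kg | +0.2% | +10.2% |
| S 80 to 72; weight 70 to 65 kg | −7.3% | −13.9% |

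The first column is a correct relative change in a percentage. It is not the relative change in kilograms of fat, which is the second column. With stable weight the two columns agree.

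**The case against.** The strongest reply is that this is a wrong unit label with little consequence. Much of that stands.

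- A reader might infer that every reported kilogram value is wrong. The article reports no plicometry value in kg. The fault lies in the rule for a planned derived variable, and if only the label is wrong the stored numbers are usable as percentages.
- A reader might infer that plicometry cannot be compared with bioimpedance or CT. Table 4 already has bioimpedance total body fat in %, so a corrected label puts the two on the same scale. For the CT estimate the article states no unit, so nothing can be concluded there.
- A reader might infer that the relative-change rule fails altogether. A relative change has no unit, and for a percentage it is computed correctly. Its divergence from the change in fat mass is a property of any percentage, including the bioimpedance one. The rule also makes the absolute discrepancies in Step 3 largely irrelevant to the planned comparison. What survives is narrower: the result is wrong only if it is presented as change in kilograms, which the present label invites.
- The illustrative values of S, age and weight are not from the documents. This affects the size of the examples, but not the missing mass term or the 0 to 100 scale.

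The reply does not remove the point itself. Condensing a fuller protocol can explain a missing detail. Here the article prints an explicit formula and states an incompatible unit twice.

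**Conclusion.** The point holds as a wrong unit for a derived variable. The formula in section 2.5.2 contains no body mass and gives a value on a percentage scale, so it cannot be kilograms of fat. Both facts follow from the printed text alone. Reading it as a percentage of body mass in particular is an inference from that scale and from the use of % for total body fat in Table 4.

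Taken as kg, the value is off by a factor of 100/weight: 1.43 at an assumed 70 kg, with agreement only at 100 kg. A relative change described as change in kg of fat is wrong whenever weight changes; in the two assumed courses it reads +0.2% instead of +10.2%, and −7.3% instead of −13.9%.

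Severity is moderate. Section 2.9 calls the analyses explorative and does not tie the sample size to this measure. Plicometry is one of several body-composition methods, and skinfolds, age and weight are all collected, so any error can be fully recovered. Whether the formula measures subcutaneous or total fat cannot be settled from the article, because the cited source is not at hand. That is a matter to check, and no error is claimed.

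**What to change.** Choose one of two routes and state it in section 2.5.2 and in the analysis plan.

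1. **Relabel (simplest).** Give the output as body fat in % of body mass, in the sentence and on the left side of the equation. No stored number changes, and the variable then has the same unit as bioimpedance total body fat in Table 4.
2. **Convert, if kg is wanted.** Compute kg = (formula output/100) × body weight from the same visit, and recompute any values already stored under the kg label. Recomputation is needed only on this route.

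On either route, check the word subcutaneous against the source cited for the formula, and apply the relative-change comparison of section 3.1.4 to the correctly labelled quantity. A change in fat percentage should be reported as such and not as a change in fat mass.

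The cost is one corrected line for route 1, or one line and a recalculation from data already collected for route 2. No new measurement is needed.

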**Figure 2 f2:**
[figure not shown]
Plicometry sites of measurement (58, 59). Skinfold measurement using the 3 point-method (1 = triceps, 2 = suprailiac skinfold; 3 = thigh).

S is the sum of the skinfold thicknesses measured at the triceps, the suprailiac skinfold and the thigh.

### 2.6 Nutritional Habits, Intake Of Food Supplements, Self-Medications, and Lifestyle

According to the guideline, a Mediterranean diet was recommended to all patients (39). Nutritional habits were assessed using a questionnaire with a focus on characteristic dietary patterns. In addition, sleeping, smoking, and drinking habits, the use of food supplements and self-medication as well as exposure to sunlight and use of sun protection were assessed using questionnaires and the self-assessment diary, respectively.

### 2.7 Biomarkers

Cancer, antineoplastic therapy as well as physical activity are closely related with biomarkers (22, 62–66).

#### 2.7.1 Blood Count, Biochemical Laboratory Markers

For disease monitoring and adjustment of the antineoplastic therapy, multiple biomarkers are routinely assessed during the quarterly study visits (**Table 5**). In addition, the BEGYN study will include vitamin D and selenium concentrations since they are often discussed as potentially relevant to cancer biology (69–72).

**Table 5 T5:** Laboratory values, intervals of assessment and reference values.

Parameter	Assessment interval	Vial	Unit	reference value
**Blood count**				
Erythrocytes	quarterly	EDTA	10\S\12/l	4.00 – 5.20
Hb	quarterly	EDTA	g/dl	12.0 – 16.0
Leukocytes	quarterly	EDTA	10\S\9/l	3.9 – 10.2
Thrombocytes	quarterly	EDTA	10\S\9/l	140 – 400
**Differential leukocyte count**				
Neutrophils rel.	quarterly	EDTA	%	42.0 – 77.0
Neutrophils abs.	quarterly	EDTA	10\S\9/l	1.5 – 7.7
Lymphocytes	quarterly	EDTA	%	25.0 – 45.0
Monocytes	quarterly	EDTA	%	2.0 – 10.0
Eosinophils	quarterly	EDTA	%	0.0 – 5.0
Basophils	quarterly	EDTA	%	0.0 – 1.0
**Biochemical parameters**				
Sodium	quarterly	Li-Heparin-Plasma	mmol/l	135 – 145
Potassium	quarterly	Li-Heparin-Plasma	mmol/l	3.5 – 5.1
Calcium	quarterly	Li-Heparin-Plasma	mmol/l	2.2 – 2.6
Magnesium	quarterly	Li-Heparin-Plasma	mmol/l	0.66 – 1.07
Iron	quarterly	Li-Heparin-Plasma	µg/dl	33 – 193
Creatinin	quarterly	Li-Heparin-Plasma	mg/dl	0.50 – 0.90
Urea	quarterly	Li-Heparin-Plasma	mg/dl	17 – 48
Uric acid	quarterly	Li-Heparin-Plasma	mg/dl	2.5 – 5.7
Glucose	quarterly	Li-Heparin-Plasma	mg/dl	60 – 100
Protein	quarterly	Serum	g/l	66 – 87
Albumin	quarterly	Serum	g/l	35 – 52
Cholesterol	quarterly	Li-Heparin-Plasma	mg/dl	<200
Triglycerides	quarterly	Li-Heparin-Plasma	mg/dl	<150
CK	quarterly	Li-Heparin-Plasma	U/l	0 – 170
ASAT	quarterly	Li-Heparin-Plasma	U/l	0 – 35
ALAT	quarterly	Li-Heparin-Plasma	U/l	0 – 35
gamma-GT	quarterly	Li-Heparin-Plasma	U/l	<40
Alkaline phosphatase	quarterly	Li-Heparin-Plasma	U/l	35 – 104
Bilirubin	quarterly	Li-Heparin-Plasma	mg/dl	<1.2
Lipase	quarterly	Li-Heparin-Plasma	U/l	13 – 60
LDH	quarterly	Li-Heparin-Plasma	U/l	0 – 262
CRP	quarterly	Li-Heparin-Plasma	mg/l	0.0 – 5.0
HbA1c	quarterly	EDTA	%	<6.0
LDL-Cholesterol	quarterly	Li-Heparin-Plasma	mg/dl	<130
HDL-Cholesterol	quarterly	Li-Heparin-Plasma	mg/dl	45 – 65
VLDL-Cholesterol	quarterly	Li-Heparin-Plasma	mg/dl	<35
Interleukin-6	quarterly	Li-Heparin-Plasma	pg/ml	<7
Selenium	quarterly	Serum	µg/l	50 – 120 (67)
Vitamin D-25-OH	quarterly	Serum	ng/ml	30 – 100 (68)
**Hormones**				
TSH	quarterly	Li-Heparin-Plasma	µIU/ml	0.27 – 4,2
fT3	quarterly	Li-Heparin-Plasma	pg/ml	2.0 – 4.4
fT4	quarterly	Li-Heparin-Plasma	ng/dl	0.93 – 1.7
Cortisol	quarterly	Serum	µg/dl	4.82 – 19.5*
Insulin	quarterly	Serum	µIU/ml	<29.1
ß-hCG	quarterly	Serum	mIU/ml	<1.0
**Tumor marker**				
CA 15-3	optional	Serum	U/ml	<26.2

^*^Reference values for Cortisol vary depending on the time of blood collection. As in the BEGYN study, samples were routinely taken in the morning these standard values were used.

#### 2.7.2 Leukocyte Subsets

Peripheral blood mononuclear cells (PBMCs) will be obtained from 9,6 ml anticoagulated blood samples by Ficoll density gradient centrifugation and resuspended in 90% fetal calf serum + 10% dimethylsulphoxide. Plasma supernatant will be collected and all biosamples will be cryopreserved at -80°C until further processing (73).

The underlying disease, the antineoplastic therapies and physical activity can have a profound impact on the immune system, respectively (26, 74–77). The number of 36 circulating leukocyte subsets will be assessed by flow cytometry using a panel of validated antibody stainings (**Table 6**), based on previous studies (73, 78). Cells will be analyzed with FACSCelesta™ (BD Biosciences, Franklin Lakes, New Jersey, USA) (79).

**Table 6 T6:** Leukocyte subsets.

population	Surface antigens
**B cells**	
innate B cells	CD19+ CD27- IgD- IgM-
naïve B cells	CD19+ CD27- IgD+ IgM+
memory B cells	CD19+ CD27+
marginal zone memory B cells	CD19+ CD27+ IgD+ IgM+
IgM memory B cells	CD19+ CD27+ IgD- IgM+
class switched memory B cells	CD19+ CD27+ IgD- IgM-
late memory B cells	CD19+ CD27+ CD38+ IgM+
plasmablasts	CD19+ CD27+ CD38^bright^ IgM-
transitonal B cells	CD19+ CD20+ CD27- CD38+
pre-naïve B cells (B1 cells)	CD20+ CD27+ CD43+ CD70-
B2 cells	CD20+ CD27+ CD43-
**T cells**	
Th cells with αβ-TCR	TCRαβ+ CD4+
cytotoxic Th cells with αβ-TCR	TCRαβ+ CD8+
memory effector Th cells	CD3+ CD4+ CD62L- CD45RO+
memory central Th cells	CD3+ CD4+ CD62L+ CD45RO+
naïve effector Th cells	CD3+ CD4+ CD62L- CD45RO-
naive central Th cells	CD3+ CD4+ CD62L+ CD45RO-
memory effector cytotoxic T cells	CD3+ CD8+ CD62L- CD45RO+
memory central cytotoxic T cells	CD3+ CD8+ CD62L+CD45RO+
naïve effector cytotoxic T cells	CD3+ CD8+ CD62L- CD45RO-
naïve central cytotoxic T cells	CD3+ CD8+ CD62L+ CD45RO-
T cells with γδ-TCR	TCR γδ+ CD3+ CD5+
naïve thymus negative Th cells	CD3+ CD4+ CD31- CD45RO-
naïve thymus negative Th cells	CD3+ CD4+ CD31+ CD45RO-
Th1 cells	CD3+ CD4+ CD183+ CCR6+
Th2 cells	CD3+ CD4+ CCR4+ CRTH2+
naïve Th1 cells	CD3+ CD4+ CD183+ CD45RO-
memory Th1 cells	CD3+ CD4+ CD183+ CD45RO+
naïve Th2 cells	CD3+ CD4+ CD45RO- CRTH2+
memory Th2 cells	CD3+ CD4+ CD45RO+ CRTH2+
regulatory T cells	CD3+ CD4+ CD25+ CD127-
**NK cells**	
natural killer cells	Lin- CD335+ CD56+ CD16+
memory-like natural killer cells	Lin- CD335+ CD56^dim^ CD16+
intermediate natural killer cells	Lin- CD335+ CD56^bright^ CD16-
innate natural killer cells	Lin- CD335+ CD56- CD16-

#### 2.7.3 Cytokine Profiles

Plasma cytokine profiles will be measured by Luminex^®^ xMAP™ technology (Austin Texas, USA) since they reflect the activity of various immune cells (**Table 7**). Luminex^®^ xMAP™ technology performed on MAGPIX™ instruments, enables the simultaneous quantification of up to 50 target proteins or nucleic acids (80) and have been validated for numerous immunological studies, including breast cancer (20, 62, 81) and infections (82). Superparamagnetic microsphere beads are conjugated with a distinct monoclonal antibody. The beads themselves are dyed with varying amounts of red and infrared fluorophores to allow clear assignment to a specific bead region. MAGPIX™ fluorescence imager-based instruments use a LED illumination/CCD camera detection system for both bead region identification and reporter fluorophore-based analyte quantification (83).

**Table 7 T7:** Cytokine profiles measures by Luminex™ (MAGPIX^®^).

Cytokine	abbreviation
Tumor necrosis factor α	TNFα
Interferon γ	IFNγ
Interleukin 1α	IL-1α
Interleukin 1β	IL-1β
Interleukin 2	IL-2
Interleukin 4	IL-4
Interleukin 6	IL-6
Interleukin 10	IL-10
Interferon γ -induced protein 10	IP10
Monocyte chemoattractant protein 1	MCP-1
Granulocyte-macrophage colony-stimulating factor	GM-CSF

#### 2.7.4 Gene Expression Profiles

The expression of selected mRNA transcripts related to breast cancer and inflammation will be measured by a quantitative real-time PCR (qPCR). The method used is based on a previously published technique (73). Total RNA will be isolated from PMBCs using the High Pure RNA Isolation Kit (Roche, Basel, Suisse). Reverse transcription will be performed using SuperScript™ VILO IV cDNA Synthesis Kit (Invitrogen, Thermo Fisher Scientific) followed by the cDNA purification using QIAquick™ PCR Purification Kit (Qiagen, Hilden). Concentration and purity determination of the isolated RNA will be performed with NanoDrop™ (Thermo Fisher Scientific, Waltham, Massachusetts, USA). TaqMan™ Gene Expression Assays (Applied Biosystems, Thermo Fisher Scientific, Waltham, Massachusetts, USA) will be used to perform qRT-PCR of immunological key transcription factors TBX21, RORC, GATA3, FOXP3 (84–88). The Δct-values will be calculated using ACTB, EEF1A1, and 18S as a standard. Values will be normalized to the data from the samples taken at the baseline visit.

### 2.8 Assessment of Psychological Parameters

The assessment of psychological parameters will be performed by using standardized questionnaires that were validated for (breast) cancer patients, respectively (89–98). A list of questionnaires is shown in **Table 8**. Moreover, the patients have the opportunity to report individual thoughts as free texts and during the study visits.

**Table 8 T8:** Assessment of the psychological parameters (used questionnaires).

Abbreviation	Name	Nmber of items	Content	Reference
**EORTC QLQ-C30**	European Organization for Research and Treatment of Cancer Quality of Life Questionnaire-Core 30	30 items	health-related quality of life (QoL)	(95)
**EORTC QLQ-BR23**	European Organization for Research and Treatment of Cancer Quality of Life Questionnaire-BReast cancer module 23	23 items	health-related quality of life (QoL) in breast cancer patients: systemic therapy side-effects, arm symptoms, breast symptoms, body image and sexual functioning	(95)
**MHS**	Mental Health Scales	76 items	willpower, acceptance of life, self-reflection, finding of a meaning, naturalness and social integration	(92)
**HADS**	Hospital Anxiety and Depression Scale	14 items	level of anxiety and level of depression	(89)
**DT**	Distress Thermometer	DT: 1 item	Psychosocial distress and possibly associated problems (practical, family, emotional, spiritual/religious and physical)	(94)
		Problem list: 39 items		
**MDWQ**	MultiDimensional Well-being Questionnaire	12 items	mood, level of alertness and level of calmness	(91)

#### 2.8.1 Quality of Life

The overall quality of life is assessed using the Quality of Life Questionnaire (QLQ-C30 version 3.0) which has been developed and validated by the European Organisation for Research and Treatment of Cancer (EORTC) to explore quality of life among cancer patients (90). The supplementary questionnaire QLQ-BR23 will be used to record symptoms specific for breast cancer (95). In sum, a score from 0 – 100 can be calculated allowing the quantification of the impairments regarding the patient’s health and quality of life.

#### 2.8.2 Mental Health

The questionnaire “Mental health scales” (MHS) (92) was used to assess the psychological integrity of the study participants, in order to evaluate the development of the patients’ personality throughout the study duration. The questionnaire consists out of seven scales (autonomy (17 items), willpower (14 items), acceptance of live (8 items), self-reflection (12 items), finding of a meaning (7 items), naturalness (10 items) and social integration (8 items)), which yields a total of 76 items. The questionnaire is answered with the help of a five-point Likert-scale (*1* = *I fully agree*; *5* = *I fully disagree*) and an example item is “Generally I am confident”.

